### Randomization, concealment of allocation, and blinding

Participants who meet the inclusion criteria will voluntarily sign an informed consent form and will be eligible for random assignment. They will be assigned randomly to the “Adjust Zang-fu and Arouse Spirit” electroacupuncture group or sham electroacupuncture group. The randomization sequence will be generated by a statistician not involved in the intervention or outcome evaluation using IBM® SPSS® Statistics version 24.0 (IBM Research Corporation, USA). The randomization numbers and group assignments will be sent immediately to the independent assessor by another research coordinator via an encrypted electronic file. As much as possible, evaluators will be prevented from communicating with the patients to avoid bias. This process will ensure that randomization concealment will be competent and unaffected by the participants or practitioners.

Due to the particularity of electroacupuncture therapy, double-blinding of the therapist and patient is not feasible. Before signing the informed consent form, patients will be told that they will receive electroacupuncture treatment. Participants will be unaware of their treatment assignment. The therapist will not be blinded but will not assess the effectiveness of the treatment. Outcome assessors, data managers and statisticians will be blinded to treatment allocation. Prior to the start of the trial, all researchers will be trained to ensure the successful implementation of the blinding procedure.

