### Outcome measures

The time schedule of enrollment, interventions, and assessments of participants are shown in Fig. 2. The following outcomes will be assessed by independent assessors.

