#### Primary outcomes

The primary outcomes include whole-brain structure and function evaluated using fMRI, metabolites in the basal ganglia evaluated using MRS, and cognitive function assessed using the MoCA and CDR.

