##### Montreal Cognitive Assessment Scale (MoCA)

This scale is an assessment tool for rapid screening of cognitive abnormalities. It is a validated scale for MCI in diabetes in China [19]. It includes 8 dimensions (attention and concentration, executive function, memory, language, visual structure skills, abstract thinking, calculation and orientation), with a total score of 30 and ≥ 26 points being normal. It is suitable for clinical applications because of its high sensitivity, coverage of important cognitive domains, and short testing time. However, it is also affected by education level, differences in cultural background, the examiner’s skills and experience in using MoCA, the environment of the examination, and emotional and mental state of the test taker will all affect the score. To correct the bias caused by education level, the total score is increased by 1 point for subjects with less than 12 years of education. This can better correct the bias caused by low education levels.

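### Group assignments are sent to a role that bears the outcome raters' label, which conflicts with the protocol's statement that outcome assessors are blinded

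*Protocol article*

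**What the plan says.** Three statements in the protocol article bear on this point.

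- **Who receives the allocation** (Randomization, concealment of allocation, and blinding): "The randomization numbers and group assignments will be sent immediately to the independent assessor by another research coordinator via an encrypted electronic file".
- **Who scores the outcomes** (Outcome measures): "The following outcomes will be assessed by independent assessors".
- **Who is blinded** (Randomization, concealment of allocation, and blinding): "Outcome assessors, data managers and statisticians will be blinded to treatment allocation".

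The sentence right after the transfer of the file turns to contact with patients: "As much as possible, evaluators will be prevented from communicating with the patients to avoid bias". On the acupuncturist, the same section says: "The therapist will not be blinded but will not assess the effectiveness of the treatment". The primary outcomes are whole-brain fMRI measures, basal ganglia metabolites from MRS, and "cognitive function assessed using the MoCA and CDR".

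**The concern.** The MoCA and CDR depend on a person who gives the scale and scores it. The protocol itself lists the examiner's "skills and experience in using MoCA" among the influences on the MoCA score. That remark is about competence, not about bias from knowing the arm, but it confirms that the examiner can move the result.

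The therapist is openly unblinded. For the comparison of real with sham electroacupuncture, protection of the two clinical primary outcomes therefore rests on blinded participants and blinded raters. If the raters hold the assignment list, one of those two protections is gone, and a difference between the arms on MoCA or CDR could partly reflect rating. The MoCA is also the outcome on which the sample size is based, so it carries particular weight.

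**Working it through.** The protocol gives no figure to reproduce here. The check is a comparison of statements.

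**Step 1: the recipient.** The file contains the randomization numbers and also the group assignments. It goes to the independent assessor. Encryption protects the file on its way but does not hide its content from the person meant to open it. Nothing says that the assignments are coded or masked for that person.

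**Step 2: the raters.** The Outcome measures section names independent assessors as those who assess the outcomes. This is the same label, in the plural. No section gives the term a second meaning that excludes rating.

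**Step 3: the blinding statement.** Outcome assessors are said to be blinded.

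**Step 4: put together.** If independent assessor means the same role in steps 1 and 2, step 3 is false for that role. If step 3 is true, the recipient in step 1 must be someone other than the raters, and the text does not say so. The protocol needs to state which holds.

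**Step 5: the neighbouring text.** The sentence after the transfer moves on to evaluators and limits their contact with patients; it does not say that the allocation is withheld from them. The closing sentence of that paragraph claims that concealment is unaffected by participants or practitioners, and does not mention assessors. Neither sentence separates the recipient from the raters.

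**Illustration of size (not part of the proof).** Suppose that electroacupuncture has no true effect, that the rater knows the arm, and that this shifts scores by d standard deviations in favour of electroacupuncture. The values of d are assumed; the documents give none.

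- Test: two-sided at 0.05 (Clinical data analysis), so 0.025 in the favourable tail. A two-sample t test of the two electroacupuncture arms is used as a simplification.
- Arm size: 24 before and 30 after the allowance for dropout (Sample size estimation).
- Noncentrality = d × √(n/2), degrees of freedom = 2n − 2. The false-benefit rate is the probability that a noncentral t exceeds the critical value.

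| n per arm | df | critical t | d | noncentrality | false-benefit rate |
|---|---|---|---|---|---|
| 24 | 46 | 2.013 | 0.2 | 0.693 | 10.0% |
| 24 | 46 | 2.013 | 0.3 | 1.039 | 17.3% |
| 30 | 58 | 2.002 | 0.2 | 0.775 | 11.5% |
| 30 | 58 | 2.002 | 0.3 | 1.162 | 20.7% |

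At d = 0.1 the rates are 5.3% (24 per arm) and 5.7% (30 per arm); at d = 0 the rate is 2.5%.

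**The case against.** The strongest reply is that the identity of recipient and rater is inferred from a label. The article is loose with role names: it speaks of an independent assessor, evaluators, outcome assessors and, under Data collecting and monitoring, a designated result evaluator. The recipient may be an allocation holder who rates nothing, and the explicit blinding sentence is the better evidence of what was intended. This stands in part. It rules out saying that the raters are in fact unblinded. It does not remove the conflict, because no section supports the harmless reading and a site would act on the words as printed. Nor is this detail that an article may leave to the full protocol: the article does name a recipient, and the one it names clashes with its own blinding claim.

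A reader might infer four further things that the documents do not support.

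- *That the limit on contact between evaluators and patients makes the scales impossible to give.* The sentence is qualified by as much as possible, so it restricts contact without forbidding administration of a scale.
- *That allocation concealment is lost as well.* This would require the recipient to screen or enrol, or to hold upcoming assignments before enrolment. Nothing says so.
- *That leaving out the acupuncturist as recipient is itself an error.* An article commonly leaves the operating route of allocation to the full protocol. The defect is the recipient that is named.
- *That the false-benefit rates estimate the bias in this trial.* They follow wholly from an assumed shift and from the premise that the rater knows the arm, which is the point in doubt.

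**Conclusion.** The point holds as an internal contradiction with a direct consequence. The protocol sends assignments to a role with the raters' label and also says that the raters are blinded. Followed literally, it would unblind whoever scores the MoCA and CDR.

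The exposure is mainly to these two scales. The fMRI and MRS results depend less on an examiner's judgement at the assessment visit, and neuroimaging processing and analysis are assigned to an outside laboratory, so they are less exposed.

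The conclusion rests on one assumption: that the same label means the same role, since no other meaning is given. It does not rest on any bias size. The range of about 10% to 21% against 2.5% shows only what would be at stake if knowing the arm moved ratings by 0.2 to 0.3 SD. Whether any rater has in fact seen the assignments cannot be settled from the document.

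**What to change.** 1. Change the recipient. Assignments go from the research coordinator, or from a named allocation holder who does no screening and no outcome scoring, only to the treating acupuncturist.
2. State that nobody who scores outcomes, manages data or analyses data has access to the allocation file. This makes the existing blinding sentence operational.
3. Use one term for the outcome rater throughout, and a different one for the allocation holder.
4. The Trial status section says that the trial is ongoing. Confirm from the transfer records who has received the file so far. If any recipient has also scored MoCA or CDR, record which participants and visits are affected and report it with the results.

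The first three items cost a few sentences and one line in the operating procedures, with no new staff. The fourth is a short audit of existing records.

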## Methods/design

### Study design

This is a randomized controlled trial. The protocol was approved by the Medical Ethics Committee of the Third Affiliated Hospital of Changchun University of Chinese Medicine (approval No. of ethics committee: CZDSFYLL2020-001-01) and registered at the Chinese Clinical Trial Registry (registration number: ChiCTR2000040268, protocol version number: V3.0, 02 October 2020.).

In this study, the tested patients will be randomly divided into two groups: an intervention group and a control group. Patients who meet the inclusion and exclusion criteria will first complete informed consent and then be randomized and stratified according to the clinical treatment. The intervention group will be divided into the “Adjust Zang-fu and Arouse Spirit” electroacupuncture group, which will be treated with electroacupuncture on a fixed prescription of acupoints, and the sham electroacupuncture group, which will be treated with electroacupuncture on nonacupuncture points and a sham instrument.

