	4b) Setting and context of treatment, including instructions to practitioners and information and explanations to patients	The study will be conducted at the acupuncture and massage center of the third Affiliated Hospital of Changchun University of Chinese Medicine. All patients will be admitted to the acupuncture therapeutic room for treatment. All information except patient allocated group will be provided to participants
**5.Practitioner background**	5) Description of participating acupuncturists	Acupuncturists who are registered Chinese Medicine Practitioners in China and have at least 3 years’ clinical experience in acupuncture practice. Besides, they went through training classes before this trial and simulation to ensure that they are able to provide identical acupuncture treatment in accordance with a pre-defined protocol
**6. Control interventions**	6a) Rationale for the control or comparator in the context of the research question, with sources that justify this choice	Based on traditional acupuncture theory, previous studies, and the consensus of acupuncturists from the third Affiliated Hospital of Changchun University of Chinese Medicine
	6b) Precise description of the control or comparator. If sham acupuncture or any other type of acupuncture-like control is used, provide details as for Items 1 to 3 above	For the Sham-electroacupuncture group: participants will receive superficial non-acupoint sham- electroacupuncture 40 sessions over 8 weeks. Non-acupoints will be needled through adhesive pads to the skin (for the fixation of needles) without penetrating the skin using 1 cun blunt needles. The needle parameters and treatment regimen are the same as for the electroacupuncture group. When turned on, electric acupuncture apparatus looks normal but has no current output

*Abbreviation*: STRICTA, Standards for Reporting Interventions in Clinical Trials of Acupuncture

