### Participants

We will recruit 90 participants from the third Affiliated Hospital of Changchun University of Chinese Medicine (Changchun, China). Before treatment, we will perform glycosylated hemoglobin A1 (HbA1c) tests, blood lipid profile indices (total cholesterol (TC), triglycerides (TGs), high-density lipoprotein cholesterol (HDL-C), and low-density lipoprotein cholesterol (LDL-C)), fMRI screens and scale assessments for the participants to select the patients to be included. For outpatients who meet the inclusion and exclusion criteria and wish to participate in the study, we will fully communicate with patients and their family members face-to-face about the trial to ensure that the patients are able to participate throughout the study.

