### Recruitment

To recruit participants, we will publicize the study through recruitment posters, scrolling electronic screens, leaflets, and WeChat public platforms. During the recruitment process, we will fully communicate with patients, clearly informing them of the purpose, significance, trial process, treatment method, and possible benefits and risks of this study. Then, we will inform patients and their guardians of the contents of the informed consent form one-by-one. When patients and their guardians completely agree with all the items in the consent form, they will sign it of their own free will.

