#### Sham-electroacupuncture treatment group

Nonacupoints will be needled through adhesive pads to the skin (for the fixation of needles) without penetrating the skin using 1 cun blunt needles. The sham electrode lines look identical to the real lines but with the inner metal wire cut off. The electric stimulators will connect the beside GV20-beside GV24, unilateral beside BL13-beside BL23, and beside SP6-beside LR3. The needle parameters were the same as those for the electroacupuncture group. When turned on the electroacupuncture instrument, the electric acupuncture apparatus looks normal but has no current output.

For both groups, the needles will be retained for 30 min for each treatment session. The participants will be treated with electroacupuncture 5 times a week, followed by a 2-day rest interval for 8 successive weeks, with 40 sessions for each patient in total.

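### Patients are told before consent that they will receive electroacupuncture, which is untrue for the sham arm and contradicts the protocol's own disclosure statements

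*Protocol article*

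**What the plan says.** Three places describe what patients are told.

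- Randomization, concealment of allocation, and blinding: "Before signing the informed consent form, patients will be told that they will receive electroacupuncture treatment". The next sentence adds "Participants will be unaware of their treatment assignment". This section does not say that patients hear of a possible sham.
- Table 1, item 4b: "All information except patient allocated group will be provided to participants".
- Recruitment: staff will communicate fully with patients, "clearly informing them of the purpose, significance, trial process, treatment method, and possible benefits and risks of this study". The consent form is then gone through item by item with patients and guardians before they sign.

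The sham procedure is set out in Table 1, item 6b, and in the sham treatment section. Non-acupoints are needled through adhesive pads "without penetrating the skin using 1 cun blunt needles". On the device: "When turned on, electric acupuncture apparatus looks normal but has no current output". The Setting section gives 30 patients to real and 30 to sham electroacupuncture, with a further 30 in the control group.

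**The concern.** The disputed sentence stands in the blinding paragraph, just before the statement that participants do not know their assignment. It therefore reads as part of how masking is to be kept. Masking requires only that the allocation be withheld. It does not require telling patients something that is false for one of the two arms.

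Consent is at stake first. A patient told everything except the allocation knows that a sham exists and can decide whether to accept that chance. A patient told only that electroacupuncture will be given cannot. These are people with cognitive impairment whose guardians also sign, and the Trial status section says the trial is under way.

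The meaning of the sham comparison is at stake second. Patients who expect active treatment for certain and patients who expect an even chance of it enter with different expectations. The protocol supports either account, so a reader of the results could not tell which one applied.

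**Working it through.** No sample-size or power calculation bears on this point. The check sets the passages side by side, with one proportion.

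**1. Is the statement true for each arm?**

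| Element | Real arm | Sham arm |
|---|---|---|
| Site | Nine named acupoints | Points beside each acupoint |
| Needle | Filiform, inserted to a stated depth | Blunt, skin not penetrated |
| Current | 0.1–1.0 mA | None; inner wire of the lead is cut |

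The statement is true for the real arm. In the sham arm there is neither needle insertion nor current, so in any sense a patient would understand, it is untrue.

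**2. How many patients does it concern?** Sham patients as a share of those assigned to a needling procedure: 30/60 = 50%. As a share of all enrolled: 30/90 = 33%. The first is the relevant share, because only these patients are offered a needling procedure.

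**3. Do the other passages agree with it?** If item 4b is followed, the existence and nature of the sham are disclosed and only the allocation is withheld. If Recruitment is followed, the trial process and treatment method are explained, and these include a sham arm. If the blinding section is followed as written, the patient is told that electroacupuncture will be given. A patient cannot both be told the full design and be told, without qualification, that the active treatment will follow. The passages conflict.

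**4. Does the statement bias the comparison between arms?** Not by itself. Study design says "Patients who meet the inclusion and exclusion criteria will first complete informed consent and then be randomized", so the same words reach both arms before assignment. The defect concerns consent and the interpretation of the sham comparison. It is not a demonstrated imbalance between arms.

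**5. Secondary check: does consent precede the screening tests?**

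- Study design and the randomization section speak of patients who meet the criteria and then sign.
- The Participants section lists HbA1c, lipids, "fMRI screens and scale assessments for the participants to select the patients to be included", and times these before treatment. It describes the full discussion for outpatients who meet the criteria.
- The Inclusion criteria make signed consent one of the criteria, for patients and for healthy subjects.

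Meeting the criteria thus presupposes consent, while consent is described as following eligibility. The order is circular. No passage places consent before screening, and none says that screening is done without it.

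**The case against.** The strongest reply is that one loose sentence is being set against two clear ones. Item 4b and Recruitment promise full disclosure except for allocation. The protocol elsewhere uses electroacupuncture as a collective term for both arms, as in Study design and in the closing paragraph on treatment sessions. The disputed sentence may be shorthand for masking. Ethics approval is on record, and the consent form is not available to check.

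Part of this stands. The documents do not show what patients actually hear, so deception in practice, or invalid consent, is not established. What does not stand is that the other passages cure the sentence. A patient cannot know the protocol's collective usage, and staff who follow the blinding section as written would give a false statement. The point concerns something the article states, so the allowance for detail left to a full protocol does not answer it.

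A reader might also infer that study blood tests, scans and scales are done before consent, so that consent comes too late and baseline data may be unusable. The documents do not support this. Signed consent is itself an inclusion criterion, Study design fixes consent only relative to randomization, and the Participants section says only that the tests come before treatment. The flow diagram and timetable, which may settle the order, are not shown. Nor do the documents support a prediction that patients will discover the sham and drop out of that arm alone: the sham leads are described as looking identical to the real ones and the apparatus as looking normal.

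**Conclusion.** The point holds as a contradiction in the protocol on what patients are told before they sign. Read as written, the sentence in the blinding section is untrue for 30 of the 60 patients assigned to a needling procedure (50%), and it conflicts with Table 1, item 4b, and with Recruitment. This rests on the plain meaning of the sentence and on the protocol's own description of the sham; no outside figure is needed. It does not rest on any assumption about the consent form, which cannot be seen. The sentence must be corrected because, if followed, it misinforms half of the treated patients in an ongoing trial.

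The order of consent and screening is a request for clarification only. No number of people tested before consent can be derived from the documents.

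**What to change.** Replace the sentence in the randomization and blinding section. Before signing, patients and guardians should be told that patients will be assigned by chance to real or sham electroacupuncture, what each involves in general terms, and that they will not be told which they receive. This is the standard that item 4b and Recruitment already set. Check that the consent form in use says the same.

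In the same amendment, reconcile Study design, Participants, Inclusion criteria and the randomization section so that they give one order: consent, study-specific screening, confirmation of eligibility, randomization.

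The cost is amended wording and an ethics amendment while the trial is running. Neutral wording may lower expectation slightly, but equally in both arms, since it is given before assignment. Masking is unaffected, because the allocation is still withheld.
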